### Sample size calculation

Accepting an alpha risk of 0.05 and a beta risk of 0.2 in a two-sided test, a total sample size of 52 patients will be required to detect a difference ≥ 10 (SD 11) units in the test of quality of life and 2 (SD 2.3) units in the PAS. In order to account for estimated 20% loss to follow-up, five patients have been added, resulting 26 patients on each group.

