#### Statistical methods

Numerical variables will be expressed descriptively as mean and standard deviation (SD). Student *t*-test for paired data will be used to compare the quantitative variables before and after the intervention, and Student *t*-test for independent samples for inter-group comparison of pre- and post-intervention changes. At a later stage, mixed models will be performed to test changes in parameters and the between-group differences in evolution, adjusting by possible confounders. The evaluation of the correlations between variables will be based on the quantitative variables obtained from the various studies and bivariate (ordered Spearman correlation) and multivariate (multiple regression) analysis. Reasons for protocol non-adherence will be registered. The level of alpha risk accepted for all tests will be 0.05.

The evaluation of the correlations between variables will be based on the quantitative variables obtained from the various studies and bivariate (ordered Spearman correlation) and multivariate (multiple regression) analysis. Reasons for protocol non-adherence will be registered and missing data will be discarded. The level of alpha risk accepted for all tests will be 0.05.

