### Repercussions of the Redyor study

Interventions to help patients confront, manage, and treat dysphagia are urgently needed. The lack of randomized controlled trials in the early diagnosis of HNC and the high number of patients lost to follow-up due to CRT side effects highlight the potential scientific contributions of this study.

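### Discarding missing data makes the change-score t-test a complete-case comparison that can be biased if losses depend on earlier swallowing; the mixed model already planned should be primary

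*Protocol article*

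**What the plan says.** In the protocol article, Statistical methods names a Student t-test "for independent samples for inter-group comparison of pre- and post-intervention changes" as the comparison between arms. It continues: "At a later stage, mixed models will be performed to test changes in parameters and the between-group differences in evolution", with adjustment for confounders that are not named. The text on correlations, non-adherence and alpha then appears twice. Only the second copy contains the missing-data rule, "Reasons for protocol non-adherence will be registered and missing data will be discarded"; the first copy has the sentence on non-adherence without it. Nothing says whether the rule also governs the mixed models.

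On loss to follow-up, Sample size calculation states: "In order to account for estimated 20% loss to follow-up, five patients have been added, resulting 26 patients on each group". Strengths and limitations repeats the figure of about 20% and presumes that losses fall equally on the two arms. Repercussions of the Redyor study refers to "the high number of patients lost to follow-up due to CRT side effects". Eligibility criteria also removes patients during the study for death, withdrawal, a disabling medical condition or inability to do the exercises. Participant timeline schedules PAS assessments from two weeks before CRT (t0) to 12 months (t6).

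**The concern.** This is a stated rule, not a detail left to a fuller document. Applied to a t-test on change, it limits the comparison to patients with both measurements. Whether completers still represent the randomised arms then depends on why the others left.

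The article gives reason to doubt that loss is unrelated to outcome. It names treatment side effects as a cause of loss in this field, and those side effects include the swallowing disturbance being measured. The reasons for loss could also differ by arm: one arm exercises before and during CRT, and the other starts after it. Equal loss rates, which the article presumes, do not ensure equal reasons. At stake is the estimated between-arm PAS difference, in a small trial where the method that could use partial follow-up is named only for a later stage.

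**Working it through.** **1. The plan's own figure.** Inputs from Sample size calculation: "Accepting an alpha risk of 0.05 and a beta risk of 0.2 in a two-sided test", and "to detect a difference ≥ 10 (SD 11) units in the test of quality of life and 2 (SD 2.3) units in the PAS".
- n per arm = 2 × [2.3 × (1.960 + 0.842) / 2]² = 20.76, rounded up to 21.
- 21 + 5 = 26 per arm, or 52 in total. Likewise 20.76 / 0.8 = 25.95, so 26.

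The 52 reproduces if it already includes the loss and the five patients are added per arm. With 21 completers per arm, power for PAS is 0.80 (normal approximation) or 0.785 (t distribution). Loss of numbers has been allowed for; what remains is who is lost.

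**2. When a complete-case change score is biased.** Assume normal data, a common SD at each visit, correlation r0 between baseline and any later visit, correlation r1 between later visits, and drop-out that depends only on PAS at the end of CRT (t3). If completers' mean t3 PAS is shifted by D in an arm, then

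shift in that arm's mean change = (r1 − r0) × D,

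and the bias is the difference between the arms' shifts. It is zero if loss is random (D = 0), if D is the same in both arms, or if r1 = r0. Otherwise it is not zero, even with equal loss rates.

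**3. Size of the bias.** The documents give no correlations or drop-out model, so these are assumed. Simulation: 4000 trials per scenario, 26 per arm, SD of change 2.3, contrast t6 minus t0, drop-out after t3. Mean complete-case estimates:

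| Scenario | r0 0.3, r1 0.6 | r0 0.3, r1 0.8 | r0 0.5, r1 0.8 |
|---|---|---|---|
| Random 20% loss, true −2 | −1.99 | −2.00 | −2.01 |
| Same t3-driven rule in both arms, true 0 | 0.00 | 0.01 | 0.00 |
| Same rule, true −2 (losses about 13–14% v 28–29%) | −1.92 | −1.87 | −1.94 |
| 20% loss in each arm, t3-driven in one only, true 0 | −0.10 | −0.19 | −0.15 |
| As above, true −2 | −2.12 | −2.17 | −2.14 |

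A likelihood-type estimate using t0 and t3 of all patients gave −1.98 to −2.02 for a true −2, and was within 0.02 of zero under the null. With equal correlation between all visits, the complete-case bias was about zero in every scenario. As a check on the formula, in the middle column the visit SD is 2.3 / √1.4 = 1.94, so a bias of 0.19 implies D = 0.19 / 0.5 = 0.38, about 0.20 SD.

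With SD 2.3 taken per visit, r0 = 0.3, r1 = 0.6 and change to t5, under the null, two further sets of simulated trials gave bias of 0.14 and 0.17 at 10%/30% loss, and 0.16 and 0.21 at 20%/20% loss informative in one arm only. The likelihood-type estimate was within 0.01 of zero. Against the 2-unit target, 0.1 / 2 = 5% and 0.2 / 2 = 10%.

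**4. Adjusting for baseline while still discarding.** In one of those sets, a baseline-adjusted analysis restricted to completers had bias of 0.25 and 0.27 in the same two scenarios (0.25 / 2 = 12.5%; 0.27 / 2 = 13.5%). A better model alone is not a remedy; the discarding has to go as well.

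**5. Precision.** Take visit SD 2.3, an assumed baseline-to-follow-up correlation r = 0.3, and 26 × 0.8 = 20.8 completers per arm.
- Change score: variance 2(1 − r)σ² = 1.40σ²; SE = √(2 × 1.40 × 5.29 / 20.8) = 0.844.
- Baseline-adjusted: variance (1 − r²)σ² = 0.91σ²; SE = √(2 × 0.91 × 5.29 / 20.8) = 0.680.
- Ratio 0.91 / 1.40 = 0.65, so 35% lower variance with the same completers.

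Under random 20% loss, the simulated SDs were 0.842 (change score), 0.683 (completers with t0 as covariate) and 0.665 (also using dropouts' t3). The last step saves 1 − (0.665 / 0.683)² = 5%; with informative loss it saved 0 to 3%.

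**The case against.** The strongest reply is that the bias is conditional and small. It needs loss that depends on earlier swallowing, acts differently by arm (through its mechanism or through a treatment effect), and unequal correlations between visits. At its largest here it is about a quarter of a standard error (0.21 / 0.85 = 0.25), and simulated type I error of the t-test stayed at 0.046 to 0.055. The correlations and drop-out models are not the trial's. All of this stands. It limits the point to a possible bias and also rules out the claim that the t-test is valid only under completely random loss.

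A second reply is that mixed models are already planned, that the first copy of the duplicated text lacks the discard rule, and that a later stage does not clearly mean a lower rank. This stands in part. The models could use partial follow-up, but nothing exempts them from the rule and nothing makes them primary. If incomplete patients are removed first, that protection is lost.

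Third, covariates, contrasts and sensitivity analyses are commonly left to an analysis plan. That is fair, and their absence is not the finding. The finding is the rule that the article does state.

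A reader might infer more than the documents support:
- That toxicity causes the expected 20% loss. The 20% is not attributed to anything; the remark on side effects concerns the field.
- That the t0 to t4 data of every dropout are wasted. No primary visit is fixed, and a patient who leaves before t4 has no t4 data.
- That discarding costs 35% of the variance. That figure comes from replacing an unadjusted change score with baseline adjustment.

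**Conclusion.** The point holds as a risk, not as a demonstrated bias. The first-named between-arm comparison is complete-case, about 20% loss is expected, and the article itself makes outcome-related loss plausible. The presumption of equal losses does not protect, because bias arose at 20% loss in each arm when the reasons differed.

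On the assumed inputs the bias is about 0.1 to 0.2 PAS units (5 to 10% of the target), and about zero under random loss, under the null with the same mechanism in both arms, or with equal correlation between visits. When one rule acts in both arms and the true effect is −2, the effect is attenuated by 3 to 7%. The separate precision loss, about 35% in variance at a correlation of 0.3, belongs to the unadjusted change score and shrinks as that correlation rises.

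These sizes rest on normal data, drop-out driven by t3 PAS alone, and the stated correlations. PAS is an ordinal scale, so they are indicative. The documents do not support a conclusion that the trial is underpowered on this account.

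**What to change.** - Delete the discard sentence and merge the two near-duplicate paragraphs into one.
- Make the mixed model already planned the primary analysis: all randomised patients, all observed visits, t0 PAS as covariate, arm-by-visit terms, and the contrast at one named visit.
- State that no patient with partial follow-up is dropped from it.
- Keep the t-test on change as supportive.
- Add one sensitivity analysis for loss that is not at random, for example assigning worse PAS values to patients lost through toxicity or death.

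The change should be dated and made before anyone sees outcomes by arm. It needs no new patients or assessments, and the 52 can stand. The cost is slightly more analysis work and reliance on a missing-at-random assumption, which the sensitivity analysis is there to probe.

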#### Monitoring

Given the non-pharmacological nature of this study, a data monitoring committee is not needed. Any adverse effect related to the exercise intervention or any unintended effect will be registered.

### Ethics and dissemination

National and international research ethics guidelines will be followed, including the Deontological Code of Ethics, Declaration of Helsinki, and current confidentiality laws concerning personal data in Spain (*Ley Orgánica 3/2018*, 5 December) and the European Union (*European Parliament and Council Regulation EU 2016/619*). Detailed, understandable oral and written information will be provided to patients and family members, and informed consent to participate will be signed by all participants (Additional file 1). The Redyor study protocol and the informed consent process have been reviewed and approved by the Clinical Ethics Committee of the Institut Hospital del Mar d’Investigacions Mèdiques, Barcelona, Spain (Comité Ètic d’Investigació Clínica Parc de Salut Mar: reference number 2015/6288/I) (Additional file 2). Standard Protocol Items: Recommendations for Interventional Trials (SPIRIT) guidelines will be followed throughout [32] (Additional file 3). This trial is supported by the Asociación Española contra el Cáncer (AECC) and was registered at www.clinicaltrials.gov with code NCT0209009911 on February 9, 2016. Amendments to the original submitted protocol are subject to further ethics review and will be communicated to investigators and participants upon approval. Investigators and sponsor will communicate trial results to participants and healthcare professionals. Manuscripts will be prepared for submission to medical journals related to this field in order to contribute to HNC knowledge.

## Discussion

Rehabilitation intervention in acute HNC patients is currently limited in Spain. Swallow disturbances are considered a side-effect during CRT, and early swallowing and speech intervention is not systematically considered. Acute side-effects are considered “*normal*” in the development of the illness and during treatment, and the Rehabilitation Department becomes involved only when a patient demands a referral or a clinician requests an evaluation; decision protocols have not yet been developed. On the other hand, there is increased interest in facing this problem, first by developing a good screening method to determine which patients require evaluation, and then evaluating new treatment techniques, including home-based training interventions. A challenge when dealing with dysphagia related to HNC is determining the clinical profile of patients who might benefit from rehabilitation interventions (e.g., IEMT). Research is urgently needed to identify the usefulness of various dysphagia screening methods and therapeutic interventions such as IEMT.

### Strengths and limitations of the study

The study has several potential limitations that must be considered. First, losses to follow-up are common in cancer studies; to address this concern, sample size estimation assumed a loss of about 20% of patients (higher than the usual 10–15% used in previous studies). We presume that these losses will affect both study arms equally. Second, the study lacks a control group; however, this design is justified by the available evidence of the benefits of swallow and speech therapy in patients with HNC-related dysphagia.

### Repercussions of the Redyor study

Interventions to help patients confront, manage, and treat dysphagia are urgently needed. The lack of randomized controlled trials in the early diagnosis of HNC and the high number of patients lost to follow-up due to CRT side effects highlight the potential scientific contributions of this study.

## Trial status

Protocol version number: Redyor_2

Begin recruitment: 03/25/2015

End recruitment: 08/21/2018

End data collection: 04/29/2019

Trial status: Enrollment is in progress; final data collection will end May 2019

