**Methods/design:**

The Redyor study is a single-blind randomized clinical trial designed to compare the effect of prophylactic oropharyngeal exercises on quality of life and dysphagia of 52 patients with HNC referred to the Radiotherapy Department. The intervention will consist of respiratory muscle training (3 times/day, 5 days/week, 21 weeks) added to the standard swallow therapy. All patients will perform the same exercise intervention, but at different times: before chemoradiotherapy (CRT; early intervention group) or immediately after completing CRT (late intervention group). The main outcome will be change in dysphagia severity assessed with the Penetration-Aspiration Scale in videofluoroscopy study; quality of life will be assessed with the EORTC-QLQ-C30 and its Head and Neck Cancer Module (QLQ-H&N35) at 3, 6, and 12 months after completing CRT.

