### Intervention

The training protocol consists of IEMT and standard swallowing exercises. Patients will be instructed to maintain a rate of 15–20 breaths/min using the Orygen-Dual® valve (described elsewhere in detail) [21, 22], a respiratory device that allows patients to train inspiratory and expiratory muscles simultaneously. Training loads will be set at a pressure equivalent to 10 maximal repetitions (if tolerated). These external pressures will be regulated weekly at 30% of maximal inspiration/expiration respiratory measures obtained. Patients will be instructed to perform 3 sets of 5 repetitions and standard swallowing exercises (mobility and tonicity exercises of the tongue, palate, larynx, and constrictor muscles), 3 times/day, 5 days/week, for 21 weeks. An experienced swallowing therapist will supervise IEMT weekly. The protocol will be the same for both groups, but one group will start 2 weeks before CRT and the other one will begin immediately after completing CRT (Fig. 1).

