### Participant timeline

Eligible patients will be randomized and referred to the Rehabilitation Department for function assessment and intervention. The study outcomes will be assessed at baseline (2-week pre-CRT, t_0_), at the beginning of CRT (t_1_), at the end of CRT (t_3_), and thereafter at 3 months (t_4_), 6 months (t_5_), and 12 months (t_6_). The Redyor schedule of enrollment is shown in Fig. 2.

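### On the stated dates, data collection closes 8.2 to 9.3 months after recruitment ends, so the visit 12 months after CRT cannot take place for the last recruits

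*Protocol article*

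**What the plan says.** The calendar is in the Trial status section of the protocol article: "Begin recruitment: 03/25/2015", "End recruitment: 08/21/2018" and "End data collection: 04/29/2019". The status line below these dates reads "Enrollment is in progress; final data collection will end May 2019".

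The visit schedule is in two places. The Methods/design paragraph of the abstract puts the quality-of-life assessments "at 3, 6, and 12 months after completing CRT". Participant timeline covers the study outcomes in general, and so the main PAS outcome too. It starts from "baseline (2-week pre-CRT, t_0") and continues "at the end of CRT (t_3_), and thereafter at 3 months (t_4_), 6 months (t_5_), and 12 months (t_6").

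The Intervention section confirms the two-week lead: "one group will start 2 weeks before CRT and the other one will begin immediately after completing CRT". The article gives no duration for CRT, and it nowhere shortens follow-up for late recruits.

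**The concern.** A patient who enters on the last recruitment day needs two weeks, then the whole of CRT, then twelve months before t6 is due. The stated calendar leaves that patient a little over eight months, or a little over nine at the latest reading of May 2019. Either a date is wrong or t6 is cut off for everyone recruited near the end.

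What is at stake is the 12-month comparison. The Sample size calculation section allows for 20% loss to follow-up, and nothing in it covers patients whose visit is impossible by design. Statistical methods says that missing data will be discarded, so these patients would drop out of a 12-month t-test. A reader of the results would also take the stated 12-month follow-up as available for all who stayed in the trial.

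The status line raises a second question. It says that enrolment is still in progress, beside a recruitment end date of August 2018, and it gives a closing month that differs from the dated entry above it.

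**Working it through.** **Inputs from the article.** Recruitment runs from 25 March 2015 to 21 August 2018. Data collection closes on 29 April 2019, or in May 2019 (taken at its latest, 31 May). Baseline is 2 weeks before CRT, and t6 is 12 months after the end of CRT. There are 26 patients per group, with 20% loss, a PAS difference of 2 (SD 2.3), two-sided alpha 0.05 and power 80%.

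**Assumptions.** CRT lasts 6 to 8 weeks, with 0 and 9 weeks as outer limits. Baseline falls on the day of recruitment; any delay would widen the gap. Accrual is even over time where a share of the window is read as patients.

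**The plan's own sample size.** For PAS, n per group = 2 × (1.960 + 0.842)² × (2.3/2)² = 20.8, rounded up to 21. Adding five per group gives 26, and so 52 in total. The stated figure is reproduced (42/0.8 = 52.5, so 53 by exact inflation).

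**Time available after the last recruitment**
- To 29 April 2019: 251 days = 8.2 months.
- To 31 May 2019: 283 days = 9.3 months.

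**Last recruit's t6** = 21 August 2018 + 14 days + CRT + 365 days

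| CRT | t6 | Days after 29 Apr 2019 | Days after 31 May 2019 |
|---|---|---|---|
| 0 weeks | 4 Sep 2019 | 128 | 96 |
| 6 weeks | 16 Oct 2019 | 170 | 138 |
| 7 weeks | 23 Oct 2019 | 177 | 145 |
| 8 weeks | 30 Oct 2019 | 184 | 152 |
| 9 weeks | 6 Nov 2019 | 191 | 159 |

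Even if the 12 months were counted from recruitment itself, t6 would fall on 21 August 2019, after both closing dates.

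**Share of accrual with no possible t6.** The accrual window is 1245 days. The number of days by which the last t6 overshoots the close equals the number of final recruitment days from which t6 cannot be reached.

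| CRT | Close 29 Apr 2019 | Close 31 May 2019 |
|---|---|---|
| 0 weeks | 128/1245 = 10.3% (5.3 of 52) | 96/1245 = 7.7% (4.0 of 52) |
| 6 weeks | 170/1245 = 13.7% (7.1) | 138/1245 = 11.1% (5.8) |
| 7 weeks | 177/1245 = 14.2% (7.4) | 145/1245 = 11.6% (6.1) |
| 8 weeks | 184/1245 = 14.8% (7.7) | 152/1245 = 12.2% (6.3) |
| 9 weeks | 191/1245 = 15.3% (8.0) | 159/1245 = 12.8% (6.6) |

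**PAS power at t6** (two-sample t-test, difference 2, SD 2.3, truncation taken as independent of other loss)
- Full enrolment, 26 per group: 87%.
- After the planned loss, 26 × 0.8 = 20.8 per group: 78%.
- With truncation of 7.7%, 20.8 × 0.923 = 19.2 per group: 75%.
- With truncation of 14.2%, 20.8 × 0.858 = 17.8 per group: 71%.

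The dates therefore account for about 3 to 7 percentage points. The fall from 87% to 78% comes from the loss already planned for.

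**Earlier visits.** The last recruit's 6-month visit falls on 17 April 2019 with 6 weeks of CRT and on 24 April with 7 weeks, both before the April close. With 8 weeks it falls on about 30 April or 1 May, just after it. The effect is mainly on t6.

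**The case against.** The strongest objection is that Trial status is an administrative block which already contradicts itself, so a mistyped date is as likely as real truncation. That stands, and it is why the conclusion is conditional on the dates and why reconciling them comes first. It does not remove the problem, because this is the article's only calendar and neither closing date fits the visit schedule.

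A reader might infer that 14% of patients lose their 12-month outcome. The article does not support so firm a figure. It rests on an assumed 7-week CRT, on the April close rather than May, and on even accrual, none of which the article settles. The two closing dates and the range of CRT lengths give about 8 to 15%.

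A reader might also infer that the sample size fails, or that the trial's power is 71%. Neither follows. The Sample size calculation section names no visit, and the main outcome is defined as a change without one. The 71 to 75% is power at one late visit, and the right comparator is the 78% that remains after the planned loss.

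Finally, the planned mixed models can use the earlier visits of truncated patients. That is a fair partial answer, provided the statement that missing data will be discarded does not remove those patients.

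**Conclusion.** Wrong as written. The stated end of recruitment, the stated close of data collection and a visit 12 months after CRT cannot all hold for the last recruits, at any length of CRT. This part needs only the article's own dates.

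The size depends on assumptions. About 8 to 15% of the accrual window is affected, or about 4 to 8 of 52 patients if accrual was even, and PAS power at t6 falls from about 78% to about 71 to 75%. The 3-month visits are unaffected, and the 6-month visits are at risk only at the margin.

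Separately, Trial status contradicts itself on whether enrolment has ended and on the closing date. If enrolment did continue past August 2018, the shortfall would be larger, but the article does not show that it did.

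**What to change.** 1. Reconcile the Trial status entries: one recruitment end date, one close of data collection, and a status line that agrees with both.
2. If the recruitment date is right, set the close at the last recruit's t6, about the end of October 2019 with 6 to 8 weeks of CRT.
3. If the close cannot move, state that t6 is administratively truncated, report the number of patients who could reach it and the number observed, by group, and keep the affected patients' earlier visits in the mixed model already planned in Statistical methods instead of discarding them.

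Making the 6-month visit primary because the cut-off allows it is not advised. It would let the closing date choose the endpoint, and with 8 weeks of CRT the last 6-month visit also misses the April close.

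The cost is a few more months of already planned visits for about 4 to 8 patients. The article appeared on 14 August 2019, after both closing dates, so this may mean reopening collection. The reporting alternative costs only wording and a less favourable stated n at t6.
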